### Data collection

Patients will be recruited from the Westmead Breast Cancer Institute, a culturally and ethnically diverse breast cancer institute in Western Sydney, New South Wales, Australia. Potential participants will be identified through physician-referral, self-referral or researchers screening past and present patient appointment lists and invited to participate. If the patient has met all inclusion criteria and none of the exclusion criteria and she has provided written, informed consent to participate, she will be enrolled in the study by a researcher.

The researcher will collect baseline participant information during a face-to-face visit at the Breast Cancer Institute, such as demographics and physical measurements (eg. BMI, body fat percentage) and participants will complete several questionnaires to assess self-reported quality of life, depression, anxiety and physical activity (see Table 1). Participants will be asked information regarding their preferred method of receiving health information and if they currently use any technologies to help them with their health, including breast cancer-specific applications. Past medical history, a list of current prescription medications and chronic disease risk factors will be collected from the participant’s medical file.

**Table 1 Tab1:** Study procedures and outcome measures collected at baseline and/or six-month follow-up assessments

	Baseline	Six-months (+/− 4 weeks)
Informed Consent	✓	
Inclusion/Exclusion Criteria	✓	
Demographics	✓	
Medical history (from hospital file)	✓	
Medication adherence (self-reported)	✓	✓
Accelerometer provided (*n* = 32)	✓	✓
Primary outcome		
Self-efficacy - Self-Efficacy to Manage Chronic Disease Scale (6-items) [35]	✓	✓
Secondary outcomes		
BMI measured by height in cm by stadiometer and weight in kilograms [36]	✓	✓
Total body fat percentage measured with Seca medical Body Composition Analyser (mBCA) 515 with Seca Analytics mBCA 115 software (Seca GmbH & Co. KG, Hamburg, Germany) [37]	✓	✓
Waist circumference in cm [36]	✓	✓
Physical activity level – GPAQ, a validated measure of mild, moderate and vigorous intense activity, as well as sedentary behaviours [38].	✓	✓
Nutrition - Questions adapted from WHO STEPS [39, 40]	✓	✓
Quality of life – measured by a core 30-item quality of life questionnaire, EORTC QLQ-30 AND	✓	✓
23-item breast cancer-specific sub-scale EORTC QLQ-BR23, which have been widely used and validated in breast cancer populations [41]	✓	✓
Illness perceptions – BIPQ, a validated 9-item measure used to rapidly assess patients’ perceptions of the cognitive and emotional impacts of their illness, including disease severity and causality [42].	✓	✓
Depression and Anxiety - short-form DASS, which has been validated and tested in numerous patient populations [43]. This scale will be collected from participants’ medical file, unless the scale was completed more than one month prior to the study visit, then participants will complete the scale.	✓	✓
Randomisation	✓	
Participant feedback survey		✓

*BMI* Body Mass Index, *WHO STEPS, World Health Organisation* STEPwise approach to chronic disease risk factor surveillance; *EORTC QLQ-30* European Organization for Research and Treatment of Cancer Quality of Life Questionnaire–Core; *EORTC QLQ-BR23* Breast Cancer subscale; *GPAQ* Global Physical Activity Questionnaire; *BIPQ* Brief Illness Perception Questionnaire; *DASS* Depression Anxiety Stress Scale

Six months after baseline, participants will be contacted to attend a face-to-face follow-up visit at the Breast Cancer Institute. Participants will be encouraged not to discuss whether they are receiving the text messages or not with the blinded researcher conducting the assessment. During this visit, researchers will repeat some of the same measurements as collected during the baseline visit, including the physical measurements and several questionnaires to assess self-reported quality of life, depression, anxiety and physical activity (see Table 1). Participants will also be asked about occurrences of any clinical events, healthcare visits and hospitalisations as well as their preferred method of receiving health information and if they currently use any technologies to help them with their health, including breast cancer-specific applications. A list of current prescription medications will be obtained from the participant’s medical file or in person, depending on availability. Finally, intervention participants will answer a survey regarding the acceptability, feasibility and utility of the text-messaging program. All data will be collected either on paper or electronic case report forms and will be monitored for quality assurance according to a pre-specified monitoring plan.

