### Outcomes

The primary outcome is self-efficacy for managing chronic disease (Table 1). Secondary outcomes (Table 1) include clinical measures (BMI, body fat percentage), lifestyle measures (physical activity, nutrition), quality of life, illness perceptions, depression and anxiety and medication adherence (self-report). We will also be collecting process measures to determine the barriers and enablers to providing a text message support program to breast cancer survivors. Participants will indicate their preferred method of receiving health information and rate the usefulness and appropriateness of the text message intervention. Any incoming text messages from participants throughout the intervention will be coded and analysed.

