## Discussion

This study aims to facilitate the transition from hospital-based care to health self-management for women with breast cancer by developing and testing a six-month lifestyle focused text message program in a RCT. This simple and cost-effective text message program uses positively-framed, informative and semi-personalised messages to motivate women to maintain healthy behaviours and remain connected with their oncology services. Expected results include improvements in primary and secondary outcomes. If successful, this study will inform a larger multi-centre RCT, with the goal of improving physical and mental health for breast cancer survivors during recovery and beyond. Results of the process measures will elucidate the barriers and enablers to widespread implementation of the text message program, with the ultimate goal of providing survivors with free, long-term out-of-hospital support after treatments.

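### Table 1 takes the DASS from the medical file if the score is up to a month old, so six-month depression and anxiety scores mix dates and settings and can precede the mediator

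*Protocol article*

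**What the plan says.** In the protocol article, the depression and anxiety row of Table 1 (Data collection) makes the file the default source of the short-form DASS: "This scale will be collected from participants’ medical file". The one exception is for an older score, since the default holds "unless the scale was completed more than one month prior to the study visit, then participants will complete the scale". The row is ticked for both baseline and six months, so the rule covers the outcome as well as the baseline covariate. The six-month column allows a window of 4 weeks either side.

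The running text of the same section reads differently. At the baseline visit, "participants will complete several questionnaires to assess self-reported quality of life, depression, anxiety and physical activity". At follow-up, "During this visit, researchers will repeat some of the same measurements as collected during the baseline visit", and the sentence goes on to include depression and anxiety questionnaires. Neither sentence mentions the medical file, though both refer the reader to Table 1.

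The Outcomes section lists depression and anxiety among the secondary outcomes. The analysis section compares each secondary outcome between arms at six months by ANCOVA adjusted for its baseline value, and plans to examine mediation by self-efficacy. The Background names anxiety and depression among the outcomes for that mediation question. Table 1 gives no file source for the self-efficacy scale.

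**The concern.** A score labelled as six-month may have been given weeks before the visit, in a clinical setting and for a clinical purpose. Other women give theirs at a research visit. Three things follow.

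- **Timing.** Some scores may be taken while messages are still being sent, which would reduce the estimated effect if benefit builds up over the programme.
- **Mediation.** A file score can predate the self-efficacy score from the visit by up to a month. For those women the outcome comes before the proposed mediator, the reverse of the order the analysis needs.
- **Source.** A recent file score at six months exists only if there was recent clinic contact, and that contact happens after randomisation. The Discussion says the messages aim "to motivate women to maintain healthy behaviours and remain connected with their oncology services", so allocation could conceivably affect who contributes a file score.

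The Table 1 rule and the running text could also lead staff to follow different procedures.

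**Working it through.** The plan states no figure on this point to reproduce. The check is timing arithmetic, followed by illustrations on assumed inputs.

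**Inputs from the protocol article**
- Follow-up visit at six months, plus or minus 4 weeks (Table 1).
- File score accepted up to one month before the visit (Table 1).
- Programme of six months at four messages per week (Study groups).
- Conversion used here: six months = 26.1 weeks, one month = 4.35 weeks.

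**Dates of six-month scores**
- All scores taken at the visit: 26.1 - 4 = 22.1 to 26.1 + 4 = 30.1 weeks, a span of 8 weeks.
- Month-old file score, visit on the nominal date: 26.1 - 4.35 = 21.75, about week 22. About 4.35 x 4 = 17 messages are still to come.
- Month-old file score, visit at the early edge: 22.1 - 4.35 = 17.75, about week 18.
- Span under the Table 1 rule: 17.75 to 30.1 weeks, about 12.4 weeks.

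The extreme case lies 26.1 - 17.75 = 8.35 weeks before the nominal date. Of that, 4 weeks (48%) come from the visit window, which applies to every six-month outcome, and 4.35 weeks (52%) from the file rule.

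**Gap between a woman's two DASS scores**
- Visit scores only: 22.1 to 30.1 weeks.
- With file scores allowed: from 17.75 weeks (baseline score at the visit, month-old file score at an early follow-up) to 30.1 + 4.35 = 34.45 weeks (month-old file score at baseline, late follow-up visit).

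**Dilution (assumed inputs).** Suppose the effect builds linearly over six months and visits fall on the nominal date. The fraction of the effect kept is then 1 - (share of file scores) x (age in months)/6.
- Share 10%, age 0.5 month: 1 - 0.10 x 0.5/6 = 0.992.
- Share 30%, age 1 month: 1 - 0.30 x 1/6 = 0.950.
- Share 50%, age 1 month: 1 - 0.50 x 1/6 = 0.917.

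Dilution is therefore about 1-8%.

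**Bias from unequal sourcing (assumed inputs).** Bias = (difference between arms in share of file scores) x (mean shift between sources, in SD).
- 10 points and 0.1 SD: 0.10 x 0.1 = 0.01 SD.
- 30 points and 0.3 SD: 0.30 x 0.3 = 0.09 SD.

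The document gives none of these shares, ages or shifts, and the direction of any bias is unknown.

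**The case against.** The strongest reply is that this is a bounded rule on one of many secondary outcomes. The one-month cap can be read as a way to spare women a duplicate questionnaire, and the primary outcome is untouched. Flagging dates and running sensitivity analyses are matters that an article commonly leaves to a fuller document. That is fair as to weight. The rule itself, however, is stated in the article and conflicts with the text around it. The running text does not cancel the rule, because it points to Table 1.

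A reader might infer that a file score captures only about two-thirds of the effect (17.75/26.1 = 68%). That is the extreme for one participant: it needs the earliest permitted visit, a full month-old score and linear build-up, and about half of the shortfall belongs to the visit window. Scheduling is described as contact at about six months. For a visit then, a month-old score falls near month 5, or five-sixths of the effect on the same assumption.

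A reader might also infer that the source of the score differs by arm. The only support is the stated aim in the Discussion. The document does not say when or why the clinic gives the DASS, so file scores may follow a schedule that messages cannot alter. The Background describes visits that become less frequent, towards annual, so recent file scores may be uncommon at six months.

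Two further limits stand. Assessor blinding does not separate the settings for a scale the woman completes herself, since she can tell in either setting whether she is receiving the messages. And baseline file scores precede randomisation, so an older one costs some precision but adds no bias.

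**Conclusion.** The point holds as a measurement-consistency defect on a secondary outcome that is also a target of the mediation analysis. Three consequences follow directly from Table 1:

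- the possible span of six-month scores widens by about a month at the early end;
- clinical and research settings are mixed;
- the outcome can precede the mediator.

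The effect on the arm comparison is probably small, with dilution of about 1-8% under the assumptions shown. Arm-dependent sourcing remains a possibility that the document neither shows nor rules out; on the assumed inputs its bias would be 0.01-0.09 SD. The share of women affected is not stated, so no firmer figure can be given. The change is worth making because it is cheap and because, if date and source go unrecorded, the problem may not be recoverable at analysis.

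**What to change.** Reconcile Table 1 with the running text by having every participant complete the short-form DASS at both study visits. Use a file score only when the visit score is missing, record its date and source, and exclude such scores in a sensitivity analysis. Visit scores would then span only the window common to all six-month outcomes and would come from the same visit as the self-efficacy score. That removes the reversed order, although mediator and outcome would still be measured together.

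The cost is a few extra minutes of questionnaire time for women who have a recent file score. No new visit or instrument is needed.

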### Data confidentiality and storage

With the participants’ consent, the research staff will collect personal information about participants in-person and via participants’ medical files, which will only be used for the purpose of this research project and will only be disclosed with the participant’s permission, except as required by law. All paper data (excluding a confidential contact form – name, DOB, mobile number, email) will be quality checked against patient files then entered into a secure password-protected server-based database, which automatically checks data ranges. Information from the contact form will be entered into an enrolment log on a secured, password-protected hospital computer. Only study researchers will have access to study data and results that will be held securely in a locked filing cabinet or on a password-protected computer in Westmead Hospital. Paper and electronic data, including the consent forms and questionnaires, will be securely destroyed (paper documents shredded, electronic data and backups permanently erased) 5 years after study results are published.

### Outcomes

The primary outcome is self-efficacy for managing chronic disease (Table 1). Secondary outcomes (Table 1) include clinical measures (BMI, body fat percentage), lifestyle measures (physical activity, nutrition), quality of life, illness perceptions, depression and anxiety and medication adherence (self-report). We will also be collecting process measures to determine the barriers and enablers to providing a text message support program to breast cancer survivors. Participants will indicate their preferred method of receiving health information and rate the usefulness and appropriateness of the text message intervention. Any incoming text messages from participants throughout the intervention will be coded and analysed.

### Process evaluation

In addition to the stated outcomes, a log will be kept of the times the text messages were sent and what proportion were delivered successfully. Moreover, a log will be kept of the number of times the participants attempted to contact the research team and the method of contact (i.e. via phone, email, text message). At the end of the blinded follow-up assessment at six-months, intervention participants will complete a study questionnaire with Likert-scaled questions to examine the acceptability and utility of the intervention. This questionnaire will include items that address the acceptability of repeated text messages, identification of which messages the participants remembered, liked or disliked, what they did with the messages (i.e., saved, shared or deleted), the perceived utility of the text messages and opinions regarding the intrusiveness, timing and content suitability of the text messages.

A subset of intervention participants will also be invited in person or via telephone to participate in a focus group to provide a more in-depth understanding of the perceived barriers and facilitators to the intervention. These participants will be purposefully selected to diversify the opinions and views shared within the group by choosing participants with ethnically, culturally and socioeconomically diverse backgrounds. Each focus group will contain approximately 8–10 people and will last approximately 60 min. A minimum of two focus groups will be conducted and will be consecutive until no new themes or categories emerge (thematic saturation). It is anticipated that at least 16–20 participants will be invited to take part and will be reimbursed for their travel and parking expenses. The focus groups will be conducted by a trained interviewer, and a discussion guide will be used to facilitate and expand the discussion around key feedback themes such as utility and acceptability of the text messages and the perceived health impacts of the intervention. The focus groups will be digitally recorded and transcribed and coded into themes using NVivo version 11.0 (QSR International). The coded data will be interpreted, to isolate key themes, contrasts and hierarchies, and to develop coding matrices based on the Framework approach [44].

### Sample size and statistical analysis plan

A mean difference of 1 unit on the average score between patients in the intervention and control groups on the Self-Efficacy for Managing Chronic Disease Scale (6 items) would be a clinically meaningful improvement. A standard deviation of 2.05 for the Self-Efficacy for Managing Chronic Disease Scale (6 items) score (an average of the six items) was published in a similar cancer population [45]. With a 20% drop out rate, 80% power and type I error of 5%, a total of 160 patients will be needed, with 80 patients in each arm (intervention: control).

All analyses will be performed according to the intention-to-treat principle by a blinded statistician. Continuous variables will be summarised as means and corresponding 95% confidence intervals (CIs), or if the distribution is skewed, as medians and interquartile intervals. Categorical variables will be summarised as frequencies and percentages. Primary outcome will be compared between the intervention and the control groups at 6-months using analysis of covariance (ANCOVA), adjusting for the baseline measure of the primary outcome. Similarly, for each of the secondary outcomes, ANCOVA, adjusting for the baseline value of the outcome, will be used to compare between the groups at 6-months. We will also investigate if changes in secondary outcomes are mediated by self-efficacy scores. A significance level of 0.05 will be used. All analyses will be undertaken using SAS 9.4 for Windows.

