### Randomisation and blinding

After the baseline assessment, participants will be randomised to either usual care (control) or the text message intervention group in a uniform 1:1 (control:intervention) allocation ratio, using a secured central computer-based randomisation service. For each participant, the computer system automatically produces a study identification number, which will be used on all study documents. Within 7 days after the enrolment visit, the computer system automatically starts sending the text message program to the participant. Therefore, the researcher conducting baseline and six-month face-to-face assessments remains blinded to treatment allocation. As an additional precaution and for safety purposes, there will be an independent, unblinded researcher monitoring all incoming text messages.

To validate the self-reported physical activity questionnaire, a subset (32/160) of participants, will be randomly assigned to wear a small (matchbox sized) accelerometer for 7 days [31] at baseline and follow-up and return it to a member of the research team.

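### On the inputs printed in the article and before baseline adjustment, a 20% loss requires 166 to 168 women, not 160; power at 160 is about 78% (minor)

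*Protocol article*

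**What the plan says.** The calculation is in the protocol article, under Sample size and statistical analysis plan. The target effect is "A mean difference of 1 unit on the average score between patients in the intervention and control groups", on the six-item self-efficacy scale. The spread comes from a published cancer population: "A standard deviation of 2.05 for the Self-Efficacy for Managing Chronic Disease Scale (6 items) score (an average of the six items"). The conclusion is "With a 20% drop out rate, 80% power and type I error of 5%, a total of 160 patients will be needed". This total is split equally into two arms of 80. Randomisation and blinding confirms equal allocation, "in a uniform 1:1 (control:intervention) allocation ratio".

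The sidedness of the test is not given; the section says only "A significance level of 0.05 will be used". The primary comparison at 6 months is made "using analysis of covariance (ANCOVA), adjusting for the baseline measure of the primary outcome". The section shows neither the evaluable number per arm nor the step that turns it into 80.

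**The concern.** The article prints a difference, a standard deviation, an error rate, a power, a dropout rate and a total in adjoining sentences, so a reader can check whether they fit together. They do not quite. If a fifth of the women are lost, 80 per arm become 64, and 64 is fewer than an unadjusted comparison on these inputs needs.

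At stake is the accuracy of the power statement for the only primary outcome. Read literally, the trial has either slightly less power than it claims or slightly less room for dropout. The Discussion says that the study is meant to inform a larger multicentre trial, so a loose dropout allowance could be carried into that design.

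**Working it through.** **Inputs.** From Sample size and statistical analysis plan: difference δ = 1, SD σ = 2.05, type I error 5%, power 80%, dropout 20%, 80 per arm. From Randomisation and blinding: 1:1 allocation. Assumed, because not stated: a two-sided test and, to begin with, no baseline adjustment.

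**1. Evaluable number per arm.**
n = 2 × (z₀.₉₇₅ + z₀.₈₀)² × σ² / δ² = 2 × (1.960 + 0.8416)² × 2.05² / 1² = 65.97, so 66. The t distribution gives 66.94, so 67.

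**2. Attempt to reproduce 160.**

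| Route | Per arm | Total |
|---|---|---|
| 66 / 0.8 = 82.5 | 83 | 166 |
| 67 / 0.8 = 83.75 | 84 | 168 |
| One-sided: 52 / 0.8 = 65 | 65 | 130 |
| 66 × 1.2 = 79.2 | 80 | 160 |
| Effect size 1/2.05 = 0.488 rounded to 0.5: 64 by t test; 64 / 0.8 = 80 | 80 | 160 |

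The first three rows use the printed inputs and miss 160. The last two reach it, but each departs from what is printed. Multiplying by 1.2 allows for a loss of 1 − 1/1.2 = 16.7%, not 20%. An effect size of 0.5 for a 1-unit difference means an SD of 1/0.5 = 2.0, not 2.05.

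**3. Power with the stated dropout.** 80 × 0.8 = 64 per arm remain.
Normal approximation: Φ(1 / (2.05 × √(2/64)) − 1.960) = Φ(2.759 − 1.960) = 78.8%. By the t test: 78.2%.

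**4. Difference detectable with 80% power at 64 per arm.**
2.05 × √(2/64) × 2.8016 = 1.015 units; by the t test 1.023. Call it about 1.02 units.

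**5. Dropout that 80 per arm can absorb at 80% power.**
1 − 66/80 = 17.5%; by the t test, 1 − 67/80 = 16.3%.

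**6. Effect of the planned baseline adjustment.** With correlation r between the baseline and 6-month scores, the SD is replaced by 2.05 × √(1 − r²). The article gives no r, so a range is shown for 64 per arm:

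| r (assumed) | Power, t | Power, normal |
|---|---|---|
| 0 | 78.2% | 78.8% |
| 0.2 | 79.8% | 80.4% |
| 0.22 | 80.2% | 80.8% |
| 0.3 | 81.9% | 82.5% |
| 0.5 | 88.5% | 89.0% |

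By the t calculation, 80% is reached at r = 0.21.

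**The case against.** The strongest reply is that the trial will not use an unadjusted test. Its primary analysis adjusts for the baseline score, and step 6 shows that a correlation of about 0.21 between two administrations of the same scale to the same women is enough to restore 80%. This stands as a limit on the conclusion. A reader might infer that the trial is underpowered; the document does not support that. What the reply does not do is make the printed sentence reproducible, because the SD quoted there is that of the score itself and no correlation is claimed.

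A reader might also infer that the dropout allowance was multiplied on instead of divided out. That would explain the figure, but the inflation step is not shown, and a correct division after rounding the effect size to 0.5 also yields 80 per arm. The document cannot separate the two, so the cause stays open.

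Nor is it a fault that the article gives no baseline correlation. A condensed article may leave that to the full protocol or analysis plan. The point rests only on printed figures that disagree with each other.

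Finally, the gap is small beside the uncertainty in an SD taken from another study and in a round 20% dropout figure. That is true, and it is why the point is minor.

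**Conclusion.** The point holds in a limited form. For a two-sided comparison without baseline adjustment, the printed inputs and a 20% loss require 166 to 168 women. The planned 160 give 78.2% to 78.8% power, a shortfall of 1.2 to 1.8 percentage points, or 6 to 8 patients (6/160 = 3.75% to 8/160 = 5%).

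Two assumptions are involved. The two-sided reading is not stated, but a one-sided reading gives 130 and does not rescue the figure. The absence of baseline adjustment matters more: under the planned analysis, 160 may well deliver 80% or more, depending on a correlation that the article does not give. The validity of the trial is not in question. The severity is minor: the sentence is inexact as written, and the sample size need not change.

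**What to change.** Keep 160 and restate the one sentence, giving the evaluable number per arm and the inflation step. Any one of these would do:

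- State that 64 evaluable women per arm after 20% dropout give about 78% power for a 1-unit difference before baseline adjustment, or 80% power for about 1.02 units.
- State that 80 per arm allow for about 16% dropout at 80% power.
- Base the power on the planned baseline-adjusted analysis and state the assumed correlation with its source. About 0.22 or more gives 80% with 64 per arm; 0.3 gives about 82% and 0.5 about 89%.

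In each case, say that the test is two-sided if that is so. The cost is one sentence. Recruitment, allocation and analysis are untouched. Under the first two options the stated power or dropout allowance becomes slightly less favourable.
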